## Study endpoints and analyses

### Primary endpoint

Primary endpoint of this study will be PFS, calculated from the time between surgery and the first event defined as recurrence or death or last follow-up. Patients still alive without recurrence at last contact are censored.

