### Study design

The PUMP trial is a phase III randomized controlled open label, multicenter trial to compare the combined efficacy of resection and/or open ablation and adjuvant HAIP chemotherapy to resection and/or open ablation alone in patients with CRC and resectable CRLM with a low CRS (0–2 points). This trial started in August 2018. Five centers participate in this study (Erasmus MC Cancer Institute, Rotterdam; Antoni van Leeuwenhoek, Amsterdam; Academic Medical Center, Amsterdam; Universitary Medical Center Utrecht, Utrecht; IJsselland Hospital, Capelle aan den IJssel). Patients will be randomized in a 1:1 ratio (Fig. 1) to resection of CRLM only (arm A), or resection of CRLM with adjuvant HAIP chemotherapy (arm B). Stratification factors will be center, number of CRLM (< 4 or ≥ 4 CRLM), and size of the largest CRLM (< 5 cm or ≥ 5 cm). Blinding is not feasible because of the nature of the intervention, including a visible subcutaneous pump. In patients who received preoperative chemotherapy for CRLM, the CRS values prior to start of preoperative chemotherapy should be used to determine eligibility. A computed tomography (CT) scan in (early) arterial phase of the liver is required prior to inclusion to determine whether intra-arterial catheter placement is technically possible. The multidisciplinary meeting should determine that complete resection of the CRLM is feasible. Resectability is defined as the opportunity to achieve an R0 resection with a sufficient liver remnant. Randomization will be performed preoperatively if the participant meets all the criteria.

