A potential subject who meets any of the following criteria will be excluded from participation in this study:presence of EHD, including positive portal lymph nodes, at the time of liver resection or any time since CRC diagnosis, with exception of small (≤ 1 cm) extrahepatic lesions which are not clearly suspicious of metastases (e.g., pulmonary lesions that are too small to characterize);second primary malignancy except in situ carcinoma of the cervix, adequately treated non-melanoma skin cancer, or other malignancy treated at least 5 years prior to inclusion without evidence of recurrence;prior hepatic radiation, resection, intra-arterial therapy or ablation;CRLM requiring two-staged liver resections;liver-first resections; but simultaneous resection of CRC and CRLM is not an exclusion criterion;(partial) portal vein thrombosis;known DPD-deficiency (heterozygous or homozygous of *DPYP*);pregnant or lactating women;history of psychiatric disability judged by the investigator to be clinically significant, precluding informed consent or interfering with compliance for HAIP chemotherapy;serious concomitant systemic disorders that would compromise the safety of the patient or his/her ability to complete the study, at the discretion of the investigator;organ allografts requiring immunosuppressive therapy;serious, non-healing wound, ulcer, or bone fracture;chronic treatment with corticosteroids;serious infections (uncontrolled or requiring treatment);participation in another interventional study for CRLM with survival as outcome;any psychological, familial, sociological, or geographical condition potentially hampering compliance with the study protocol and follow-up schedule.

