## Treatment strategies

### Standard procedures in control arm (arm A)

Patients included in the study should undergo surgery within 6 weeks after signing the informed consent. Local treatment (resection and/or open ablation) of the CRLM in both arms is in accordance with the national guidelines. An intra-operative ultrasound evaluation of the liver will be performed to assure the feasibility of complete resection of the CRLM with an adequate liver remnant. Resection of CRLM can be performed either by minimal-invasive (laparoscopic or robotic) or open approach at the discretion of the surgeon.

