### Investigational procedures of the experimental arm (arm B)

The treatment of patients randomized to the experimental arm consists of HAI pump placement following complete resection and/or open ablation of all CRLM. Pump implantation will be cancelled in patients with unexpected unresectable CRLM or EHD detected at the time of surgery. Implantation of the HAI pump (Tricumed IP2000V infusion pump; Fig. 2) is performed by an open or minimal-invasive approach. In patients requiring simultaneous resection of the primary tumor and CRLM, the colorectal resection is performed after pump placement to reduce the risk of pump contamination. The implantation procedure of the infusion pump and dose adjustment protocols have been discussed by previous authors and was optimized for the materials used in this trial [14, 15]. In addition to local treatment of the CRLM, a cholecystectomy is performed to avoid cholecystitis as a result of inadvertent intra-arterial chemotherapy of the gallbladder [16]. The pump catheter is positioned in the gastroduodenal artery (GDA) allowing perfusion of the entire liver without obstructing the flow in the hepatic artery. The pump catheter has rings at the distal end that allow for securing the catheter with non-absorbable ties in the GDA (Fig. 3). In patients with abnormal hepatic arterial anatomy, the GDA is still the preferred site, as long as it connects with a proper hepatic artery perfusing at least one segment of the liver. Perfusion of the entire liver can be achieved in these patients by ligating all accessory and replaced hepatic arteries. Intrahepatic shunts will typically reassure that the catheter perfuses all liver segments.

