### Secondary endpoints

Secondary endpoints include: OS (calculated from surgery until death from any cause; patients still alive at last contact are censored), hepatic PFS, safety, quality of life (EQ-5D + QCQ-C30), and cost-effectiveness. Furthermore, the pharmacokinetic profile of intra-arterial administration of floxuridine will be investigated in more detail. Moreover, we aim to identify predictive biomarkers (circulating tumor DNA) for the efficacy of HAIP chemotherapy. Finally, the accuracy of CT angiography will be evaluated compared to radionuclide scintigraphy to detect extrahepatic perfusion.

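### PFS and OS start at surgery although randomisation is preoperative, so never-operated patients have no time zero, and disease found uncleared at surgery is not a PFS event

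*Protocol article*

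**What the plan says.** All references are to the protocol article.

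- **Study design:** "Randomization will be performed preoperatively if the participant meets all the criteria". The trial is open label.
- **Standard procedures in control arm:** "Patients included in the study should undergo surgery within 6 weeks after signing the informed consent".
- **Primary endpoint:** PFS is "calculated from the time between surgery and the first event defined as recurrence or death or last follow-up", followed by "Patients still alive without recurrence at last contact are censored".
- **Secondary endpoints:** "OS (calculated from surgery until death from any cause; patients still alive at last contact are censored".
- **Investigational procedures of the experimental arm:** "Pump implantation will be cancelled in patients with unexpected unresectable CRLM or EHD detected at the time of surgery".
- **Study population:** one exclusion criterion is "presence of EHD, including positive portal lymph nodes, at the time of liver resection or any time since CRC diagnosis". Its first limb can be settled only after the patient has been randomised.

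The article gives no start date for a randomised patient who is not operated on, and no rule for how disease that was never cleared counts towards PFS.

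**The concern.** A clock that starts at surgery suits an adjuvant trial that randomises after resection. Here allocation comes first, and reaching surgery and being cleared are both post-randomisation outcomes. Two groups are affected in different ways.

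1. **Never operated on** (progression, death or withdrawal before surgery): no time zero exists, so neither PFS nor OS can be computed.
2. **Operated on but not cleared** (unresectable or extrahepatic disease found at surgery): the clock starts and death counts, but the only disease event is recurrence. The endpoint is called progression-free survival, yet progression is not in its definition.

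What is at stake is the comparison of the groups as randomised. Allocation is known before surgery and only arm B faces pump implantation, so withdrawal before surgery, or the judgement that disease is unresectable, could differ by arm.

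**Working it through.** **Step 1. Apply the definitions to each kind of randomised patient.**

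| Patient | PFS start | Disease event | Death counts in PFS | OS |
|---|---|---|---|---|
| Cleared at surgery | surgery | recurrence | yes | defined |
| Operated on, not cleared | surgery | none that fits | yes | defined |
| Never operated on | none | none | no start date | no start date |

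**Step 2. Reproduce the plan's own figures** (Sample size calculation: HR 0.60, two-sided 0.05, 80% power, medians 17 and 17/0.60 = 28.3 months, 36 months accrual plus 12 months follow-up, 5% dropout).

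- Events (Freedman): (1.960 + 0.842)² × [(1 + 0.60)/(1 − 0.60)]² = 7.85 × 16 = 125.6, so 126. This matches.
- Event probability per arm: 1 − [exp(−12λ) − exp(−48λ)]/(36λ), with λ = ln 2/median. This gives 0.679 and 0.504, mean 0.591.
- Patients: 126/0.591 = 213; 213/0.95 gives 225. The accrual route gives 6 × 36 = 216 and 216/0.95 = 228 after rounding up. Both are within 3% of 230.

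The sample size is not in error. Moving the time origin does not change the 126 events.

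**Step 3. Size of the recurrence-only rule.** The article gives no rate of uncleared patients, so every share below is an assumption. Simulated Cox hazard ratios use 400,000 patients, exponential PFS, control median 17 months, 36 + 12 months, and an assumed median time to death of 20 months in uncleared patients.

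| True HR in cleared patients | Uncleared A / B | Event at surgery | Counted only at death | Dropped |
|---|---|---|---|---|
| 0.70 | 10% / 10% | 0.74 | 0.73 | 0.70 |
| 0.60 | 5% / 5% | 0.63 | 0.62 | 0.60 |
| 0.60 | 10% / 10% | 0.65 | 0.63 | 0.60 |
| 0.70 | 5% / 10% | 0.79 | 0.72 | 0.70 |
| 0.60 | 5% / 10% | 0.69 | 0.62 | 0.60 |

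The figures vary by about 0.01 between runs. With equal shares, counting uncleared patients only at death rather than as events at surgery shifts the HR by about 0.01, and by up to about 0.02 at the design HR with 10% uncleared. The large gaps in the last two rows come from the assumed imbalance.

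**Step 4. Cost of counting uncleared disease as an event, equal shares u.** This assumes that HR 0.60 holds in cleared patients and that uncleared patients contribute events with HR 1. Patients after dropout: 230 × 0.95 = 218.5. Average HR = exp[(cleared events / all events) × ln 0.60].

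- u = 5%: cleared events 218.5 × 0.95 × 0.591 = 122.8; uncleared 218.5 × 0.05 = 10.9; total 133.7; HR 0.626.
- u = 10%: 218.5 × 0.90 × 0.591 = 116.3; uncleared 21.9; total 138.2; HR 0.650.

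Power (Schoenfeld) = Φ(√d × |ln HR|/2 − 1.96). At d = 126 this is 82% for HR 0.60, 75% for 0.626 and 68% (0.675) for 0.650. At the expected totals of 134 and 138 events it is 77% and 71%.

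**Step 5. Cost of dropping patients instead.** If 5% or 10% left the analysis on top of the 5% dropout, expected events would fall from 129 to 123 or 116. Freedman power, Φ(√d × 0.40/1.60 − 1.96), would be 79% or 77% at HR 0.60.

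**The case against.** - **An unseen analysis plan may settle who is analysed.** This is true of the analysis set, and the article nowhere says that anyone is excluded. That such patients will be dropped is an inference, not a stated rule. But the time origin and the event are stated here, and an intention-to-treat sentence elsewhere would not give an unoperated patient a surgery date.
- **Recurrence may be condensed wording for an endpoint named progression-free survival.** This is possible. It is a reason to write the definition out, since the literal text scores persistent disease as event-free.
- **A reader might infer that all uncleared patients lack a valid outcome.** They do not: operated patients have a surgery date, a full OS and a death event in PFS. Only the disease event fails.
- **A reader might infer a large bias, for example an HR of 0.79 rather than 0.70.** That needs 5% uncleared in arm A and 10% in arm B. No rate is given, local treatment follows the same guidelines in both arms, and the stated reasons for cancelling the pump are tumour findings, not effects of the pump. Differential loss is possible, but a doubling is unsupported.
- **A reader might infer unequal censoring because arm B has two-weekly blood monitoring.** The CT schedule is the same in both arms (Follow-up), and the two-weekly monitoring lasts only for the six 4-week cycles. Any effect is confined to early losses and is minor.
- **Listing last follow-up among the events** is a drafting slip, because the next sentence censors those patients.

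**Conclusion.** The point holds in a limited form. As written, PFS and OS are undefined for randomised patients who never reach surgery, and the PFS disease event is undefined for patients whose disease is not cleared, a group the protocol itself foresees. The analysis therefore does not compare the groups as randomised.

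The direction and size of any bias cannot be derived from the article. With equal shares of 5–10% uncleared (assumed), the recurrence-only rule alters the HR by only about 0.01 to 0.02. Larger shifts require unequal losses, which are also an assumption. The article does not support saying that treatment failures will materially inflate the result. The planned 126 events and 230 patients stand as computed.

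The definition should still be corrected before outcomes are compared by arm, because it decides who enters the primary comparison and from when.

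**What to change.** 1. Define PFS and OS from randomisation, for all randomised patients by allocated arm.
2. Define the PFS event as the first of: recurrence or progression; unresectable disease, extrahepatic disease or incomplete clearance, dated when found; or death from any cause.
3. Keep the from-surgery analysis in resected patients as a sensitivity analysis.
4. Remove last follow-up from the list of events.
5. Optional and minor: censor PFS at the last CT without recurrence.

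**Cost:** wording in the protocol and analysis plan, with no new data. PFS and OS times will include the preoperative interval in both arms. Counting uncleared patients as events dilutes the effect, from HR 0.60 to about 0.63–0.65 under equal 5–10% shares, with about 75–68% power at 126 events against 82% by the same formula. The plan should state this loss, together with the share of uncleared patients that it expects.

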## Sample size calculation

A median PFS of 17 months was observed in 228 low-risk patients with resectable CRLM at Erasmus MC treated between 2000 and 2012, without EHD (consistent with arm A). In a multivariable analysis using a consecutive cohort of 779 low-risk patients without EHD, treated with or without HAIP chemotherapy between 2000 and 2012 at MSKCC, a hazard ratio (HR) of 0.60 (95% CI: 0.49–0.75) was found. Given a HR of 0.60 (corresponding to a median PFS of 28 months in arm B), 80% power and a 2-sided significance level α = 0.05, a total of 126 events need to be observed. With an expected accrual rate of 6 patients per month in five centers, 3 years accrual and one additional year of follow-up, and taking into account a drop-out rate of 5%, a total of 230 patients need to be randomized. No interim analysis is planned for survival outcomes.

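### PFS and OS start at surgery although patients are randomised before it, so a randomised patient who is never operated on has no time zero

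*Protocol article*

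**What the plan says.** All references are to the protocol article.

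- **Start of the clock.** Under Primary endpoint, PFS is "calculated from the time between surgery and the first event defined as recurrence or death or last follow-up". Under Secondary endpoints, OS is "calculated from surgery until death from any cause".
- **Allocation.** Under Study design: "Randomization will be performed preoperatively if the participant meets all the criteria". The same section says: "Blinding is not feasible because of the nature of the intervention, including a visible subcutaneous pump".
- **Gap to surgery.** Under Standard procedures in control arm (arm A): "Patients included in the study should undergo surgery within 6 weeks after signing the informed consent".
- **Findings at operation.** Under Investigational procedures of the experimental arm (arm B): "Pump implantation will be cancelled in patients with unexpected unresectable CRLM or EHD detected at the time of surgery".
- **Design figures.** Sample size calculation assumes a control median of 17 months, a hazard ratio of 0.60, 80% power and two-sided α of 0.05. It gives 126 events and 230 patients, with a 5% drop-out allowance that is not defined further.

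The article gives no other start date for a patient without surgery and names no analysis population. Analysis of the primary endpoint announces Kaplan-Meier curves for the whole group and for each arm.

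**The concern.** Randomisation makes the arms comparable at the moment of allocation. Here the clock starts later, at an event that not every randomised patient need reach, and by then patient and surgeon know the arm. Someone who progresses, dies, becomes unfit or withdraws before the operation has no PFS or OS time under the stated definitions, so nothing can be entered in the Cox model for that person. Read literally, the primary comparison is of operated patients.

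If reaching surgery were related to arm, the PFS and OS hazard ratios would no longer estimate the effect of assigning HAIP chemotherapy. If it were unrelated to arm, some early failures would still be missing from both curves.

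**Working it through.** **1. The plan's own figures.** Freedman's formula gives events = (z₀.₉₇₅ + z₀.₈₀)² × ((1 + HR)/(1 − HR))² = (1.960 + 0.842)² × (1.6/0.4)² = 7.85 × 16 ≈ 126, as stated.

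For the number of patients, take exponential PFS with medians of 17 and 17/0.60 = 28.3 months, uniform accrual over 36 months and 12 further months. The event probabilities are then 0.679 and 0.504, with mean 0.591. So 126/0.591 = 213.04, rounded up to 214, and 214/0.95 gives 226. Alternatively, 6 per month × 36 = 216, and 216/0.95 gives 228. Both are close to 230. None of the stated design figures is wrong, and none is tied to a start date in the calculation.

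**2. Who lacks a time zero.** A patient found unresectable or with extrahepatic disease at operation has a surgery date, so the clock is defined. Only patients randomised and never operated on lack one. Their number is not given. As a range, 2%, 5% and 10% of 230 are about 5, 11.5 and 23 patients.

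**3. Effect on power if they are lost.** Scale the 126 events by the share retained and use power = Φ(√events × 0.4/1.6 − 1.96):

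- 2% lost: 123.5 events, 79.3%
- 5% lost: 119.7 events, 78.1%
- 10% lost: 113.4 events, 75.9%

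With all 126 events it is 80.1%. Lost power is the smaller issue.

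**4. Effect on the hazard ratio.** This is a simulation with 115 patients per arm, uniform accrual over 36 months and data cut at month 48. Surgery is 0.25 to 1.4 months after randomisation. PFS after surgery is exponential, with a 17-month control median and a true hazard ratio of 0.60 unless noted. The numbers not operated on and what happens to them are assumptions. The 6-week limit runs from consent, and the simulation applies it from randomisation.

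| Not operated on (A v B) | Their course | HR from surgery, operated only | HR from randomisation, all |
|---|---|---|---|
| 0 v 0 | – | 0.60 | 0.60 |
| 6 v 6 | all progress within 1.4 months | 0.61 | 0.63 |
| 3 v 6 | same | 0.60 | 0.65 |
| 3 v 8 | same | 0.60 | 0.67 |
| 2 v 10 | same | 0.60 | 0.71 |
| 6 v 6, true HR 1 | same | about 1.0 | about 1.0 |
| 2 v 10, true HR 1 | same | 1.00 | 1.11 |
| 6 v 6 | half progress, half censored early | 0.59 | 0.61 |
| 3 v 6 | same | 0.60 | 0.62 |
| 2 v 10 | same | 0.60 | 0.65 |
| any of these splits | all withdraw event-free | no difference | no difference |

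Rows in which all progress used 1,500 replicates, and rows with half progressing used 600. A repeat run agreed within about 0.02, so shifts of that size are near the simulation's precision.

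**5. Scale of the balanced shift.** ln(0.63/0.61) = 0.032. With 126 events the standard error of the log hazard ratio is about 2/√126 = 0.18. The shift is about 0.2 standard errors.

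**6. If everyone is operated on.** Up to 6 weeks, or 6/4.345 = 1.4 months, is added to both curves. The medians become at most 18.4 and 29.7 months, and the hazard ratio stays at 0.60 (first row).

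**The case against.** Surgery is the usual origin for recurrence in an adjuvant setting, and a condensed article may leave the analysis population and the handling of missing surgery dates to a fuller document. The announced curves for the whole group may even suggest that everyone was meant to be included. It stands that exclusion follows from the wording and is not a written rule. A reader might infer that the plan removes never-operated patients from the primary and OS analyses, but no sentence says so. What the article does fix is the origin, for both endpoints. Naming an intention-to-treat population would not supply the missing date.

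A reader might also infer that arm B waits longer for surgery because of pump planning. The documents do not support this. The early arterial phase CT is required of every patient before inclusion, and a single 6-week limit is stated for patients included in the study.

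Nor is unequal non-operation shown to be likely. Local treatment follows the same national guidelines in both arms. A patient who refuses the pump, or is disappointed by arm A, can still have the operation and so has a start date. The greater burden of arm B makes imbalance conceivable, but no rate is given. The 2 v 10 split has no basis in the text, and early progression in every non-operated patient is a worst case.

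Finally, a patient who withdraws before surgery adds almost nothing under either clock, so dating from randomisation does not recover that information. The 5% drop-out allowance replaces lost numbers and does not address selection.

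**Conclusion.** The mismatch is certain from the text: allocation before surgery, arm known, both survival endpoints counted from surgery, and no substitute date. Never-operated patients are undefined for PFS and OS, and events before surgery are not counted.

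Material bias is possible but not demonstrated. It depends on how many patients are not operated on, whether this differs by arm, and whether they progress early. With about 5% not operated on and all progressing within about 6 weeks, the hazard ratio moves from about 0.61 to 0.63 if balanced, and by more if unequal. It is essentially unchanged if there are no such patients or if all leave event-free. A reader might take the larger shifts, such as 0.60 to 0.71, as an estimate of the bias in this trial. They only illustrate what an extreme imbalance would do. With no true effect and a balanced split, both clocks give about 1.0, so balanced non-operation does not create a false positive.

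The point still deserves correction because it concerns the primary endpoint, the number affected cannot be known in advance, and the remedy is cheap.

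**What to change.** In the sections Primary endpoint and Secondary endpoints:

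- Define PFS and OS from the date of randomisation for all randomised patients, analysed in the arm assigned.
- State one PFS event rule, the same in both arms, for every patient not rendered disease-free. It should cover those never operated on and those found unresectable or with extrahepatic disease at operation. A rule for the first group alone would leave the second unscored.
- Report the number not operated on by arm.
- Keep the surgery-based clock as a sensitivity analysis and for comparison with the 17-month historical median.

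This should be settled before outcomes are compared by arm. It needs a short amendment and a date that the trial records in any case. The stated targets of 126 events and 230 patients do not change.

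The cost is medians up to about 6 weeks longer than on the surgery clock, and a hazard ratio that may be slightly less favourable. If 5% of patients carried no treatment effect, for example, the hazard ratio would be 0.60^0.95 = 0.616, and 126 events would give about 76% power by the formula above. That would reflect the effect of assignment, which is what the randomised comparison should estimate.
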